## Abstract

The present study aimed to investigate the effects of balance training associated with cerebellar tDCS on postural control in individuals with PD. This is a randomized clinical trial in which individuals were allocated to an experimental group (EG) or placebo group (PG), in which a conventional protocol of 10 Physiotherapy sessions for locomotor training and postural control was applied. In the EG, tDCS was applied, with a current setting of 1.5 mA for 20 min simultaneously with postural control training. In the PG, tDCS was applied in sham mode, with the same electrode positioning and the same number of sessions as the EG. The sample compared 34 individuals with PD (EG: 17; PG: 17).Cerebellar tDCS associated with balance training may help improve postural control and balance in walkers with Parkinson's Disease. The hypothesis is, if walking improve, the benefits may be accompanied by better balance and reduced fear of falling, and individuals may experience greater free-living physical activity at home and in the community.

Specifications table

**Table utbl0001:** 

Subject area:	Neuroscience
More specific subject area:	**TRANSCRANIAL DIRECT CURRENT STIMULATION (tDCS) ASSOCIATED WITH BALANCE TRAINING IN INDIVIDUALS WITH PARKINSON'S**.
Name of your protocol:	**EFFECTS OF TRANSCRANIAL DIRECT CURRENT STIMULATION (tDCS) ASSOCIATED WITH BALANCE TRAINING IN INDIVIDUALS WITH PARKINSON'S: STUDY PROTOCOL FOR A RANDOMIZED CLINICAL TRIAL**
Reagents/tools:	tDCS: Neuromodulator from Microestim Foco Research, NKL, Santa Catarina, Brazil. Baiobit Movement Analysis® (BTS Bioengineering S.P.A., Italy) All acceleration data will be recorded by sampling at 100 Hz frequency, transmitted to a notebook via Bluetooth and processed by the Rivelo software program (BTS Bioengineering Group, S.P.A., Italy
Experimental design:	A prospective, randomized controlled trial with concealed allocation, blinded assessors (participants and therapists), and intention-to-treat analysis will be carried-out (Figure 1). Community-dwelling people with PD will be recruited from the general community, by means of advertisements and by screening reference outpatient clinics. Participants of both sexes will be included, regardless of age, with a clinical diagnosis of PD, classified as 3 or 4 Hoehn & Yahr scale^18^, and who agreed to participate in the study with consent. Individuals with neurological disorders other than PD and with cognitive deficits that prevented them from carrying out the assessments were not included, and individuals with scores lower than 8 on the 10-CS were not included^19^
Trial registration:	Brazilian Registry of Clinical Trials (RBR-52y3zgd
Ethics:	The study was conducted in line with recommendations from the Declaration of Helsinki and received ethical approval from the Ethics Committee of the Federal University of the Amazonas, Brazil [CAAE 54,743,121.5.0000.5020].
Value of the Protocol:	Cerebellar tDCS associated with balance training may help improve postural control and balance in walkers with Parkinson's Disease. The hypothesis is, if walking improve, the benefits may be accompanied by better balance and reduced fear of falling, and individuals may experience greater free-living physical activity at home and in the community. The goal of protocol is to investigate the effects of balance training associated with cerebellar tDCS on postural control in individuals with PD.

## Background

The reduction or insufficiency of dopamine in Parkinson's disease (PD) triggers significant impacts on the extrapyramidal system, manifesting itself through symptoms such as tremors, plastic hypertonia, bradykinesia, freezing and decreased postural reflexes [1]. These manifestations tend to result in disturbances in balance, gait and postural control. As consequence, increases falling risk and a deterioration in the quality of life of affected individuals [2,3].

Several therapeutic approaches are used in the treatment of PD, with emphasis on pharmacological[4] and surgical interventions [5]. Furthermore, it is important to highlight that physical exercise is supported by a substantial level of evidence in the therapeutic management of individuals affected by PD [6]. This approach demonstrates the ability to improve several aspects affected by the disease, covering issues related to physical capacity, inactivity, gait, posture, transfers, balance and fall prevention [6,7]. Physical exercise has the potentially improves both motor aspects, such as gait, balance and strength, as well as non-motor aspects, such as depression, apathy, fatigue and constipation, associated with PD. Furthermore, it may contribute to the mitigation of secondary complications resulting from immobility, such as cardiovascular problems and osteoporosis [8,9].

Among the resources available for the treatment of impairments linked to PD is Transcranial Direct Current Stimulation (tDCS). In general terms, tDCS consists of the application of low-intensity direct electrical current (1–4 mA) through two surface electrodes: a cathode (negatively charged) and an anode (positively charged). This approach differs from Transcranial Magnetic Stimulation (TMS), which consists of applying short-duration magnetic pulses to induce electrical currents in the brain [[10], [11], [12], [13]]. tDCS produces a potential difference between the applied electrodes, thus generating changes in the neuronal membrane potential that is located within the resulting electric field. The effect produced depends on both the direction of the current (anodal or cathodal) and the axonal orientation, resulting in neuronal depolarization or hyperpolarization. In general, anodal tDCS tends to increase neuronal excitability, while cathodal tDCS tends to decrease it [11,12,14].

The cerebellum plays a relevant role in motor control [15]. It is related to the control of the vestibular system, proprioception, cognition and motor programming, receiving visual and auditory input and sending efferent fibers to the thalamus, red nucleus and cortex (motor, pre-motor and pre-frontal cortex) [16]. tDCS has been widely used in the motor cortex, however, Mello [17] suggests that applying tDCS in the cerebellar region could be an alternative to stimulate the efferent pathways of the cerebellum to act on the cortical structures involved in motor processing and, in this way, influence the motor learning process [17].

Therefore, the objective of the present study is to investigate the effects of a balance training program associated with cerebellar tDCS on postural control in individuals with PD.

The specific research questions are:•In people with Parkinson's Disease, is balance training associated with tDCS superior to balance training alone for improving walking (balance, postural control), mobility and falls?•Are any benefits maintained beyond the intervention period?

## Description of protocol

Methods details

## Ethical approval

The study was conducted in line with recommendations from the Declaration of Helsinki and received ethical approval from the IRB of the Federal University of the Amazonas, Brazil [CAAE 54,743,121.5.0000.5020].

## Sample size and subject recruitment

For the sample calculation, the primary outcome was the total MiniBESTest value. The value of the minimum clinically significant difference is 3.4 points in the total MiniBESTest value [18]. Using this value, for the statistical calculation of ANOVA two-way (between-within factors) an effect size of 0.25 Cohen's F was found. Therefore, we calculate using an effect size of 0.25 Cohen's F, type I error (alpha) of 5 %, type II error (beta) of 80 %, 2 groups, 3 moments (before training, after training and follow-up) and a correlation between repeated measurements of 0.5. After the calculation we arrived at the value of 14 patients per group. Accepting the possibility of 20 % possible sample loss, the selection of 17 patients per group was considered. For the calculation, the statistical software G*Power 3.1 (Universitat Kiel, Kiel, Germany) was used.

Community-dwelling people with PD will be recruited from the general community, by means of advertisements and by screening reference outpatient clinics. Participants of both sexes will be included, regardless of age, with a clinical diagnosis of PD, classified as 3 or 4 Hoehn & Yahr scale [19], and who agreed to participate in the study with consent. Individuals with neurological disorders other than PD and with cognitive deficits that prevented them from carrying out the assessments were not included, and individuals with scores lower than 8 on the 10-CS were not included [20]. The study was written based on the CONSORT checklist [21] and included a total of 4 stages: Initial assessment (AV1), Intervention, Immediate Post-intervention Assessment (AV2) and Reassessment (follow-up) (Fig. 1). After providing a signed consent form, individuals were invited to participate in the assessment and intervention protocols described below.

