### Blinding and randomization

The randomization will be generated by computer by an independent researcher not involved in the recruitment process or in the application of the intervention protocol, through randomization in blocks of 4, in order to guarantee balance in terms of the number of participants between the groups, being: experimental (EG), who received the balance training protocol associated with the application of tDCS, or placebo (PG), who received the balance training protocol associated with tDCS-placebo.

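### Two sample-size figures are misstated: the type II error is printed as 80%, and 17 per group covers a loss of 17.6%, not 20%

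*Protocol article*

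**What the plan says.** All the figures are in the protocol article, section Sample size and subject recruitment.

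- Outcome: "the primary outcome was the total MiniBESTest value".
- Effect size: "we calculate using an effect size of 0.25 Cohen's F".
- Error rates: "type I error (alpha) of 5" per cent and "type II error (beta) of 80" per cent.
- Design: "2 groups, 3 moments (before training, after training and follow-up").
- Correlation: "a correlation between repeated measurements of 0.5".
- Result: 14 per group, from G*Power 3.1.
- Loss allowance: 20%, described as "possible sample loss, the selection of 17 patients per group was considered".

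The article gives no separate power figure, so the printed beta is the only statement of the power target.

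**The concern.** Both figures conflict with the calculation they belong to.

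Power is one minus the type II error, so a type II error of 80% is 20% power. Anyone who enters the printed value will not get 14 per group, and nothing else in the article tells them which number to trust.

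The allowance for loss is meant to ensure that 14 per group remain after one in five is lost. Seventeen per group does not do that: 80% of 17 is 13.6.

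At stake is whether the paragraph that justifies the trial's size can be reproduced, and whether its statement about attrition is true. The validity of the analysis is not in question.

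**Working it through.** **Inputs, all from the sample-size section:** f = 0.25; alpha = 0.05; k = 2 groups; m = 3 measurements; correlation ρ = 0.5; loss 20%; 14 per group before the allowance and 17 after it.

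**Assumptions the article does not state:** the test is the group-by-time (within-between) interaction, and the non-sphericity correction is epsilon = 1.

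**Formula (repeated-measures ANOVA, noncentral F):** λ = f² × N × m / (1 − ρ), df1 = (k − 1)(m − 1) = 2, df2 = (N − k)(m − 1).

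**Step 1. Reproduce the 14 per group.** For N = 28, λ = 0.0625 × 28 × 3 / 0.5 = 10.5 and df2 = 52, which gives power 0.812. For N = 26, λ = 9.75 and df2 = 48, which gives 0.778. The smallest balanced total that reaches 0.80 is therefore 28, or 14 per group, an exact match.

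**Step 2. Take the printed beta literally (power 0.20).** N = 6 gives 0.184 and N = 8 gives 0.258, so 8 participants in total would be enough. That is far from 28.

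**Step 3. Try other terms of the same ANOVA.** The main effect of time gives the same totals as the interaction: 28 at power 0.80 and 8 at power 0.20. The main effect of group needs 86 at power 0.80 and 16 at power 0.20. No term gives 28 with beta at 80%.

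**Step 4. Reproduce the 17 per group.**

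- Multiplying: 14 × 1.2 = 16.8, rounded up to 17. This is the stated figure.
- Dividing, as needed to keep 14: 14 / (1 − 0.20) = 17.5, rounded up to 18.
- Check: 17 × 0.8 = 13.6, below 14; 18 × 0.8 = 14.4, which keeps 14.
- Loss that 17 per group really covers: (17 − 14) / 17 = 3/17 = 17.6%.

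**Step 5. Power at the stated loss.** 34 × 0.8 = 27.2. Losses come in whole patients, so exactly 20% cannot occur.

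| Lost of 34 | Loss | Analysed | Power |
|---|---|---|---|
| 0 | 0% | 34 | 0.888 |
| 6 | 17.6% | 28 | 0.812 |
| 7 | 20.6% | 27 | 0.795 |
| 8 | 23.5% | 26 | 0.778 |

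At the fractional value 27.2 the formula gives 0.799. Power at 20% loss is therefore 79.5% to just under 80%.

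**The case against.** The strongest reply is that neither slip matters to the trial. The wrong beta never entered the calculation, because 14 per group reproduces exactly at 80% power. The loss allowance is short by 0.4 of a patient per group, and power at 20% loss is within about half a percentage point of 80%. The assumed correlation matters at least as much: with 28 analysed, a correlation of 0.48 instead of 0.50 also gives 0.795, and 0.45 gives 0.771. All of this stands, and it sets the size of the point. It does not make the printed figures correct.

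Three stronger readings are tempting, and the document does not support them.

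- *The trial was planned with 20% power, or is too small.* The stated 14 rules out 20% power, and with full retention 34 participants give 0.888.
- *Power falls to about 78% at the loss the plan allows.* That figure belongs to 26 analysed, a loss of 23.5%, which is beyond the stated allowance.
- *Blocks of 4 are inconsistent with 34 participants.* The randomisation is "through randomization in blocks of 4", and 34 is eight full blocks and a half block. The worst split is 18:16. The section on blinding and randomisation aims at balance in numbers and does not promise exactly 17:17, so there is no error here.

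Raising the number to 18 per group would also satisfy the 20% allowance. However, the article says that data analysis is under way, so this may no longer be possible, and the size of the gap does not call for it.

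**Conclusion.** The point holds as two misstated figures in one paragraph. The type II error should be 20%, not 80%, and the number per group is unaffected. The 17 per group protects 14 only up to a loss of 17.6%; at the stated 20%, about 27 of 34 remain and power is about 79.5%, marginally below 80%. The power figures rest on the stated f and correlation, on the interaction as the tested term, and on epsilon = 1. The beta contradiction and the inflation arithmetic do not depend on the last two: no term of the ANOVA yields 28 at 20% power, and 17 × 0.8 is below 14 in any case. The effect on the trial is small. The reason to act is that the stated figures are wrong and cost almost nothing to correct.

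**What to change.** In the sample-size section:

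1. Replace the error-rate wording with *power 80% (type II error, beta, 20%)*. The 14 per group stays.
2. Keep 17 per group and do one of the following: restate the tolerated loss as about 17% (3 per group; 17.6% exactly, rounded down so that it is not overstated), or keep 20% and add that power would then be about 79.5% with 27 analysed.

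It would help to name the tested term (group-by-time interaction) and the epsilon used, if these match the G*Power run, so that a reader can repeat it. The cost is two edited sentences and a slightly less favourable statement on attrition or power. Enrolment, randomisation and analysis do not change.

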**Fig. 1 fig0001:**
[figure not shown]
Illustrative figure of the methodological stages of the study.

## Subject data collection

Informed consent was obtained from every subject enrolled in the study.

Measurements and interventions will be conducted during the on phase of medication. Analyses of inclusion criteria, getting informed consent, data collection, and statistical analyses will be carried out by researchers, who will be blind to group allocation. All the participants will be evaluated and receive all the information regarding the interventions in a research laboratory. The study obtained ethical approval from the Institutional Research Ethical Committee (CAAE 54,743,121.5.0000.5020) of the *Universidade Federal do Amazonas*, Manaus, Brazil. The trial was prospectively registered at the Brazilian Registry of Clinical Trials (RBR-52y3zgd).

### Assessment

The initial assessment consisted of sociodemographic data and health information of the participants, being carried out via telephone contact using a Google Forms form as a form of screening, together with assessments of the severity of the disease using the Hoehn & Yahr, cognitive level through the 10-Point Cognitive Screener and the perception of physical activity level through the International physical activity questionnaire (IPAQ). The variables of interest for sociodemographic and health data will be: age, sex, education, income, fear and occurrence of falls, freezing and duration of illness.

Postural control performance will be assessed using MiniBESTest [18]. Individuals underwent the 10-meter walk test to assess gait performance [[22], [23]]. For each participant, 3 collections will carry out, and the arithmetic mean of the recorded variables will considered for analysis. The individual was instructed to walk at their usual speed.

The variables of interest were: speed (m/s), cadence (steps/min), stride length (meters), step length (meters), step duration (seconds), support phase (% of the cycle), swing phase (% of cycle), individual support. Gait performance assessment data will be recorded by Baiobit Movement Analysis® (BTS Bioengineering S.P.A., Italy), a portable wireless inertial system with wearable sensors, which weighs 37 g and measures 70 × 40 × 18 mm, composed of a triaxial accelerometer (16 bits/axes) with multiple levels of sensitivity (±2, ±4, ±8, ±16 g), a triaxial gyroscope (16 bits/axes) with multiple sensitivity levels (±250, ±500, ±1000, ±2000°/s) and a triaxial magnetometer (13 bits, ± 1200 µT). To assess gait, the device is fixed with a semi-elastic belt to the posterior region of the pelvis of the subject being examined, approximately at the level of the L5-S1 vertebrae.

All acceleration data will be recorded by sampling at 100 Hz frequency, transmitted to a notebook via Bluetooth and processed by the Rivelo software program (BTS Bioengineering Group, S.P.A., Italy) [24,25].

Baiobit will be also used to evaluate the final phase of MiniBESTest, which includes carrying out the normal and dual-task Timed up and go (TUG test) (TUG DT) (subtraction of 3 by 3), with 3 collections also being carried out. The variables of interest will be the duration of the test (time), duration of the phases: sitting to standing, turning back, turning to sitting and standing to sitting.

### Blinding and randomization

The randomization will be generated by computer by an independent researcher not involved in the recruitment process or in the application of the intervention protocol, through randomization in blocks of 4, in order to guarantee balance in terms of the number of participants between the groups, being: experimental (EG), who received the balance training protocol associated with the application of tDCS, or placebo (PG), who received the balance training protocol associated with tDCS-placebo.

## Primary outcome measurements

The device used for tDCS was the Microestim Foco Research (NKL, Santa Catarina, Brazil). The devices has 2 types of stimulation: Real and Sham, the latter being a simulation of electrical stimulation, but which does not completely provide the stimulus to the patient. This technique is also known as “placebo stimulation” and aims to make the patient believe that they are receiving real stimulation, although the energy provided by the equipment is significantly lower than the energy provided by a normal-type stimulus.

To access Normal or Sham type stimulation on the equipment, the operating Physiotherapist enters a valid Use Code made up of 5 numbers. Microestim has 200 use codes, 100 codes for use with the real stimulation and 100 codes for the sham stimulation. These codes being provided to Physiotherapists by the independent researcher, ensuring the blinding of everyone involved in the research. Participants were identified by codes, to guarantee confidentiality throughout the research process.

### Intervention

In both groups, a conventional Physiotherapy protocol will be applied for locomotor training and postural control, based on the study of exercises [6] for the trunk and lower limbs, using a metronome, during the “on” time of the medication, with the aim of training semi-static and dynamic balance, provided by 10 sessions, spread over 4 weeks (Week 1: 3 sessions; Week 2: 3 sessions; Week 3: 3 sessions; Week 4: 1 session).

To apply tDCS, the individual was positioned sitting on a chair and the electrodes were inserted into sponges with saline solution, fixed with an elastic band. The anode electrode was positioned in the cerebellar region (OZ)^26^, and the cathode in the frontal region (fp1, fp2) [26], according to the International System 10–20 for insertion of Electroencephalography (EEG) electrodes [27,28].

After parameterization, the device will be attached to the patient's waist in a transparent material bag to visualize proper functioning. In the EG, tDCS was applied, with a current setting of 1.5 mA for 20 min, added to an initial period of 10 s of current rise and a final period of 10 s of current descent, simultaneously with postural control Training.

In the PG, tDCS was applied in placebo mode, with the same electrode positioning and the same number of sessions as the EG, however, the device remained in sham mode.

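### The stimulator stays in view during training, and the use codes said to ensure blinding do not conceal what it shows: a possible, avoidable risk to participant and therapist blinding

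*Protocol article*

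**What the plan says.** All references are to the protocol article.

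- **Intervention:** once it has been set up, the stimulator is worn at the waist "in a transparent material bag to visualize proper functioning". In the experimental group the current runs for 20 minutes, with 10 seconds of rise and 10 seconds of descent, at the same time as the postural control training. The placebo group has the same electrode positions and the same number of sessions, with the device in sham mode. Both groups have 10 sessions over 4 weeks.
- **Primary outcome measurements** (where the device is described): to select the mode, "the operating Physiotherapist enters a valid Use Code made up of 5 numbers". On supply, "Microestim has 200 use codes, 100 codes for use with the real stimulation and 100 codes for the sham stimulation". In sham mode, "the energy provided by the equipment is significantly lower than the energy provided by a normal-type stimulus". The claim that follows is "These codes being provided to Physiotherapists by the independent researcher, ensuring the blinding of everyone involved in the research".
- **Specifications table, experimental design:** the blinding statement reads "blinded assessors (participants and therapists", closing the parenthesis there. The wording is unclear, but it names both of the parties who are present while the device is worn.
- **Subject data collection:** those who screen for inclusion, collect data and analyse are stated to be blind to allocation.
- **Sample size and subject recruitment:** the initial assessment, the post-intervention assessment and the follow-up are stages separate from the intervention. The primary outcome is the MiniBESTest total.

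**The concern.** The article makes an unqualified blinding claim and supports it with the use codes. It then chooses to keep the device visible for the express purpose of watching it work. If anything the device displays, lights or sounds depends on the mode, the participant and the physiotherapist can learn the arm during the session, whatever the code concealed at the start.

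The trial compares real with sham stimulation on top of the same training, so its conclusion depends on the current being the only difference between the arms. A participant who believes the stimulation is real may try harder. A physiotherapist who knows the arm may coach differently. Both influences act during training, and a blinded assessor at a later visit cannot remove them. A difference in MiniBESTest could then not be attributed to the current with confidence, yet the trial would still be reported as blind for everyone.

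**Working it through.** The article gives no figure on blinding to reproduce, so the check sets its statements side by side.

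1. **What the code conceals.** The code is five digits supplied by someone outside the treatment team. If the physiotherapist cannot tell real codes from sham codes, the mode is hidden at entry. Nothing about the code governs what the device shows once it is running.

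2. **What is in view, and for how long.** The sentence on the bag is not limited to one group. In the experimental group, 10 sessions × 20 minutes = 200 minutes of stimulation per participant with the device visible. The placebo group has the same 10 sessions.

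3. **Whether the view reveals the mode.** There are two cases.
   - If display, lights and sounds are the same in both modes, watching the device shows only that it is on, and the claim stands.
   - If they differ, participant and physiotherapist can tell the arm.

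   The article describes no display and does not say which case applies.

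4. **Who could see it.** The participant wears it, and the physiotherapist works beside the participant. The bag is described only for intervention sessions. Assessments are separate stages, done by researchers stated to be blind. The article does not say that assessors see the device or that treating physiotherapists score the MiniBESTest.

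5. **How it could reach the primary outcome.** Two routes remain: participant expectation and effort, and therapist coaching. A third, scoring by someone who knows the arm, would need assessors to be unblinded, and nothing in the article shows that.

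6. **Whether the code supply forces sharing between participants.**
   - Sessions per arm: 17 × 10 = 170, against 100 codes per mode. A new code for every session is not possible, but the article does not call for one.
   - One code per participant: 17 × 1 = 17 of 100.
   - Five codes per participant, each used twice: 17 × 5 = 85 of 100.

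   Reuse within one participant tells the physiotherapist nothing about anyone else. The supply therefore allows every participant to have private codes. The article states no rule either way.

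**The case against.** The strongest reply is that the decisive premise is absent. Unblinding needs a visible difference between modes, and none is described. The device has a purpose-built sham mode meant to make the patient believe the stimulation is real, and seeing that it runs is not seeing its mode. Lower energy is simply what sham means and is no evidence that anyone can tell the modes apart. The codes are also not the only safeguard: allocation is concealed, an independent researcher generates the sequence and supplies the codes, electrode placement and session number match, and data collectors and analysts are blind. A condensed article may also leave the device panel to the full protocol.

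Most of this stands, and it rules out several stronger readings that a reader might infer:

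- **That the blind is shown to have failed.** It is not. The text leaves a risk open and does not contradict itself.
- **That the primary outcome is scored with bias.** Assessors are stated to be blind and work at separate stages. The article does not state that the MiniBESTest is examiner-scored, and its final phase is also recorded by a sensor.
- **That 170 sessions against 100 codes creates a leak.** Only sharing between participants would leak, and the supply does not force it.
- **That randomisation "through randomization in blocks of 4" makes later allocations predictable.** That needs earlier arms to be known already to someone who can influence enrolment, and those who judge inclusion are stated to be blind.
- **That the bias can be put in MiniBESTest points.** The article gives no basis for such a figure. Setting an assumed drift against the 3.4-point minimum clinically significant difference would only restate the assumption.

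What the reply does not remove is that visibility is a stated design choice, not an omitted detail. It is set beside a claim that blinding of everyone is ensured, and the mechanism offered for that claim does not cover what can be seen during the session.

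**Conclusion.** The point holds as an uncontrolled and avoidable risk to the blinding of participants and treating physiotherapists. Its reach is every one of the 10 sessions in both groups. Its size in points on the primary outcome cannot be derived from the documents.

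The conclusion rests on two readings: that the device is worn in the bag in both groups, and that the physiotherapist who delivers training can see it. It becomes an actual failure only if the visible or audible indication differs by mode, which the article neither states nor excludes. If a check shows the modes are the same, the claim needs one supporting sentence and the concern closes. If they differ, the claim to have blinded everyone cannot stand as written.

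**What to change.** 1. **Check the device once.** Run it with one real and one sham code and record whether display, lights and sounds are the same from start to end. State the result in the protocol and the trial report.
2. **Cover it during sessions.** Replace the transparent bag with an opaque pouch that has a flap for function checks. The downside is small: the continuous view of the device is lost, and function is checked by lifting the flap.
3. **Match the claim to the result.** If the modes differ visibly, or if sessions are already complete and the modes differed, restate the blinding claim to cover only those who could not see the device. The Abstract speaks of 34 individuals compared and Protocol validation says that data analysis is ongoing, although tenses are mixed throughout. The pouch may therefore come too late for some or all participants. The check and the restatement remain possible in any case.
4. **Keep codes private to a participant.** Give each participant codes that are used for no one else. This is a free precaution and fits the 100 codes per arm, for example five each (85 per arm).

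Asking participants and therapists to guess the arm, and varying the block size for anyone not yet randomised, are optional additions. The total cost is a pouch, one short device check and a code list, with no extra visits or staff.
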